### Interim analyses {21b}

The trial has no interim analyses or stopping rules.

### Methods for additional analyses (e.g., subgroup analyses) {20b}

Generalized logistic models will be used to examine the relationships among pre-pregnancy changes in weight, eating, activity, and physiology, and GDM recurrence; we will follow the approaches outlined by Kraemer et al. [164] to explore the potential mediators of the treatment outcome.

### Methods in analysis to handle protocol non-adherence and any statistical methods to handle missing data {20c}

Under intention-to-treat principles, all participants with confirmed pregnancy will be included in the primary analysis. If study measured OGTT results are not available, provider assessments will be used (based on chart abstraction). Missing data related to outcomes will be evaluated to assess whether the missing mechanism may be ignorable or non-ignorable [165–167]. If the missing data mechanism is judged to be ignorable, where appropriate, analyses involving mixed models may be used such that all existing values are analyzed, and no observations are deleted due to missing values. Alternatively, multiple imputations may be carried out to create several complete data sets. For each complete data set, overall tests of interest for the outcome will be conducted and the results of each combined to create a single test result. For completeness, a pattern missing analysis will be conducted to investigate non-ignorable missingness. If the missing data mechanism is likely to be non-ignorable, multiple imputations can be conducted using a version of the approximate Bayesian bootstrap based on distance-based selection criteria [168]. Sensitivity analyses under various assumptions regarding the missing data will be conducted to confirm the robustness of the results.

### Plans to give access to the full protocol, participant level-data {31c}

Upon publication of the study’s pre-specified outcomes, a de-identified version of the database will be made available upon reasonable request to the PI.

## Oversight and monitoring

### Composition of the coordinating center and trial steering committee {5d}

The primary decision-making body of this study is the investigative team comprising the principal investigator (PI, [name]), the Miriam Hospital site PI ([name]), and the co-investigators. The PI and site PI are responsible for the overall management of the study. They coordinate the operations of the study, review issues that arise in the conduct of the study in between investigative team deliberations, and bring issues to the investigative team for decision. The PI ([name]) serves as the liaison with the funding body, including submission of annual reports and providing overall management of the fiscal and administrative operations, and is also responsible for the study coordination and implementation at the Cal Poly site. The site PI ([name]) is responsible for the study coordination and implementation at the Miriam Hospital site.

The project coordinators (PCs) at each site are responsible for the day-to-day operations of the study, including recruitment, data collection processes, and intervention process. The PCs also coordinate IRB revisions and data monitoring reports and document completion of the trainings. The PCs work closely with each site’s budget analyst, research office, and investigators to ensure staff workload and progress are aligned with the budget. Research assistants (RAs) are responsible for recruiting and screening the participants, obtaining informed consent with participants, and scheduling and conducting follow-up assessments. Interventionists at each site are responsible for the treatment implementation. The data manager creates the data tracking system and supervises the development of the study’s REDCap surveys.

### Composition of the data monitoring committee, its role, and reporting structure {21a}

The trial includes two external safety officers with expertise in clinical trial weight control research and maternal/fetal health. Twice per year, safety officers review the reports of recruitment, retention, fidelity, and safety information on all participants, including the number of pregnancies before the 4-month intervention is over, number of injuries due to physical activity, number of miscarriages, and other serious adverse events. Weekly internal investigator meetings also occur to review the recruitment, attendance, retention, and safety data on an ongoing basis.

### Adverse event reporting and harms {22}

Adverse events (AEs) include any event that causes or increases the risk of harm to the participant or others. Serious adverse events (SAE) include any event that results in death, inpatient hospitalization or prolongation of existing hospitalization, a persistent or significant disability or incapacity, or a congenital anomaly or birth defect. A fatality, including fetal, is reported within 24 h. AEs reported at core assessment visits or informally at any time are evaluated by the research team and the investigators to determine if they are unanticipated problems involving risk to subjects and others or not. The participant’s situation is also assessed with regard to study and/or intervention continuation. Any SAEs are recorded by the research coordinator, reported to the PI and investigative team, the safety officers, and the IRB.

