### Intervention descriptions {11a}

#### Group 1: Standard care + education

Women in this condition receive usual medical care before and during pregnancy and throughout the trial. Also, these women meet with a study interventionist for 20-min individual sessions at study entry and again after 16 weeks. The first meeting at study entry encourages women to spend the next 16 weeks improving overall health before pregnancy and reviews nutrition (e.g., consuming multivitamins, folic acid) and physical activity recommendations. The second face-to-face meeting occurs after 16 weeks and focuses on managing stress and also includes a *Pregnancy Primer*. Since all women in the study have expressed a desire to have another pregnancy within 1–3 years, this module provides participants with standard information on methods to track ovulation. Participants also receive information on the recommended amount of weight gain [118] during pregnancy. Throughout the study, women receive quarterly study newsletters with study updates and general information about preconception health and wellness.

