##### Format and contact

The intervention focuses on ongoing, individual contact with a study interventionist to promote weight loss prior to conception. Visits may be conducted in person, on the phone, or through video conferencing. For the first 16 weeks, participants meet weekly for ~ 30 min. Thereafter, participants meet bi-weekly (or more frequently in the context of weight regain) to maintain weight loss until conception. After conception, intervention contacts are discontinued.

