##### Exercise goals

Participants are instructed to increase their physical activity to at least 150 min per week during the initial 16-week program (e.g., 30 min per day, 5 days per week). Thereafter, they are advised of higher goals (60 min/day) to promote long-term weight loss maintenance. Brisk walking, “child-friendly,” and inexpensive activities are suggested, taking into consideration potentially unsafe neighborhoods. Participants are provided with a pedometer and encouraged to gradually increase the number of steps they walk per day (with an increase of ~ 250 steps/day each week) until reaching an ultimate goal of about 10,000 steps per day [122].

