#### Process measures

Recruitment, eligibility, refusal rates/reasons, and retention rates/reasons are tracked, as well as the number of women who conceive during the trial and the average duration until conception. Intervention acceptability is measured based on participants’ ratings of various aspects of the program, the interventionist, content, and overall impression. To measure intervention fidelity, all intervention sessions are audiotaped, and a randomly selected subset (10%) is coded for content by a trained study staff (not involved in any assessment data collection). Adherence to the intervention is measured via attendance at treatment sessions, number of self-monitoring records returned, and the activity, eating, and behavioral measures. To assess the safety of the intervention, levels of hunger, depressive symptoms, injuries due to physical activity, changes in medical status, and unintended reduction in milk supply (in breastfeeding women) are assessed.

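### Adverse events from scheduled visits and from informal reports are pooled although contact differs greatly by arm, so by-arm counts of minor pre-conception events would be hard to interpret

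*Protocol article*

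**What the plan says.** All references are to the protocol article.

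- **Source of adverse events.** *Adverse event reporting and harms {22}*: "AEs reported at core assessment visits or informally at any time are evaluated by the research team and the investigators". The purpose given is to decide whether an event is an unanticipated problem and whether the participant should continue.
- **Contact, intervention arm.** *Format and contact*: "For the first 16 weeks, participants meet weekly for ~ 30 min", and then "Thereafter, participants meet bi-weekly (or more frequently in the context of weight regain) to maintain weight loss until conception". The section adds: "After conception, intervention contacts are discontinued".
- **Contact, control arm.** *Group 1: Standard care + education*: these women "meet with a study interventionist for 20-min individual sessions at study entry and again after 16 weeks". The intervention arm also receives everything that Group 1 receives.
- **Common assessments.** *Participant timeline {13}* gives both arms major assessments by masked assessors at baseline, 16 weeks, 26 weeks' gestation and 6 weeks postpartum, with brief assessments in between until conception.
- **Safety items.** *Process measures*: "To assess the safety of the intervention, levels of hunger, depressive symptoms, injuries due to physical activity, changes in medical status" and reduced milk supply are assessed. Table 3 schedules process measures at 4 months and every 4 months until pregnancy, without distinction by arm.
- **Use.** *Composition of the data monitoring committee {21a}* has two safety officers review, twice a year, counts that include early pregnancies, activity injuries, miscarriages and other serious events.

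**The concern.** An informal route records whatever a participant happens to mention to study staff. If one arm has many more conversations with staff, it has many more occasions to mention a sprain, a fall or a short illness. The rule on adverse events adds such reports to those from core visits and does not ask for the source to be kept. The section on process measures and Table 3 do provide a common schedule for the safety items, but the adverse event section does not name those visits as a source.

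The events most exposed are minor, soon forgotten and close to what the intervention sessions discuss. Activity injury is the clearest example. It matters because after week 16 the activity goal changes in the intervention arm ("Thereafter, they are advised of higher goals (60 min/day) to promote long-term weight loss maintenance"), so injury is an event for which a reader will want a fair comparison. If counts by arm are drawn from the pooled source, an excess in the intervention arm could be only ascertainment, and a real excess could be dismissed as such.

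**Working it through.** The article states no contact total and no adverse event rate, so there is no figure of its own to reproduce. The contacts follow from the schedule.

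**Inputs.** Intervention sessions: one a week for 16 weeks, then one every two weeks until conception (*Format and contact*, reading bi-weekly as every two weeks). Control sessions: 2 (*Group 1*). Common assessments: baseline, 16 weeks and every 16 weeks after that until conception (*Trial design {8}*). Full attendance is assumed.

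**Interventionist sessions.** For a woman who has not conceived by week H (H ≥ 16), the intervention count is 16 + (H − 16)/2, and the control count is 2.

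| Weeks without conception | Intervention | Control |
|---|---|---|
| 16 | 16 | 2 |
| 26 | 16 + 10/2 = 21 | 2 |
| 52 | 16 + 36/2 = 34 | 2 |
| 104 | 16 + 88/2 = 60 | 2 |
| 156 | 16 + 140/2 = 86 | 2 |

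**All study contacts in 52 weeks.** Common assessments fall at weeks 0, 16, 32 and 48, which is 4 in each arm. The totals are 34 + 4 = 38 against 2 + 4 = 6. If the two shared education sessions are held separately in the intervention arm, they are 40 against 6.

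**What this could do to a count (illustration only).** Suppose that true event rates are equal, that events fall evenly over 52 weeks, and that an event is recorded only if a study contact follows within w weeks. The windows w are assumptions; the article gives none. Controls are covered for w weeks before each of the visits at weeks 16, 32 and 48, so their captured share is 3w/52 for w up to 16. Intervention contacts are never more than two weeks apart, so for w of 2 or more the captured share is 100%.

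| Assumed window w | Intervention | Control | Apparent ratio |
|---|---|---|---|
| 2 weeks | 100% | 6/52 = 12% | 52/6 = 8.7 |
| 4 weeks | 100% | 12/52 = 23% | 52/12 = 4.3 |
| 8 weeks | 100% | 24/52 = 46% | 52/24 = 2.2 |
| 16 weeks | 100% | 48/52 = 92% | 52/48 = 1.1 |

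If only the common visits counted, each arm would have 4 ascertainment points in that year, and the captured shares would be equal whatever the window.

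**Which events the mechanism reaches.**

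- *Early pregnancies:* pregnancy tests follow the same schedule in both arms (Table 3). Largely protected.
- *Miscarriages:* intervention contacts end at conception, so the contact gap largely closes once pregnancy is recognised. Largely protected.
- *Depressive symptoms:* a scheduled measure in both arms, with brief behavioural and psychosocial measures at the every-4-month visits (Table 3). Largely protected.
- *Perinatal outcomes:* taken by chart abstraction in both arms (*Maternal/infant consequences of GDM*). Protected.
- *Activity injuries and minor medical events before conception:* scheduled as safety items every 4 months, but informal reports are added on top. Exposed.

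**The case against.** The best defence is that the quoted sentence is not a rule for comparing arms. It governs case-by-case review for the protection of participants, and for that purpose reports should be accepted at any time. The article states no between-arm test of adverse events and does not say that the safety officers see counts by arm. This stands, and it limits the point to any by-arm summary that is produced.

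The second defence is that the items meant to judge the safety of the intervention are already collected on a common schedule. This also stands. What it does not do is keep informal reports out of the same count, and the adverse event section does not name that schedule as a source.

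The third is that 34 against 2 overstates the contrast. It leaves out the shared assessments, assumes full attendance and applies only to women who do not conceive within the year. All correct; 38 against 6 is the fairer figure, and it is still a wide gap. It is also true that the article nowhere says that informal reports come mainly through interventionists. Research assistants schedule and conduct assessments in both arms and may hear such reports too.

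Some stronger readings are tempting but not supported:

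- *Adverse event collection is informal only between week 16 and 26 weeks' gestation.* This equates the undefined core visits with the major assessments and overlooks the safety items scheduled every 4 months until pregnancy.
- *About 76 women (0.30 × 252) have no structured safety follow-up after week 16.* The 30% mixes women lost to follow-up, whom no visit schedule reaches, with non-pregnant women who still have brief visits.
- *Early pregnancies, miscarriages and psychiatric events will be over-counted in the intervention arm.* As set out above, these largely fall outside the mechanism.

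**Conclusion.** The point holds in a limited form. As written, the adverse event section pools solicited and informal reports while pre-conception contact differs by design: 38 contacts against 6 in a 52-week year without conception, with full attendance. By-arm counts of minor pre-conception events, chiefly activity injuries and minor medical events, would be open to differential ascertainment and hard to interpret in either direction.

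The size of any distortion cannot be computed from the article. The range of about 1.1 to 8.7 rests wholly on assumed recall windows and equal true rates. With a window as long as the 16-week visit interval, the effect nearly vanishes. The documents do not show that the safety comparison as a whole is biased, and the primary efficacy analysis is not affected.

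**What to change.** 1. In the adverse event section, name the existing 4-month and every-4-month safety items (*Process measures*, Table 3) as a source of adverse events, asked with the same structured questions in both arms by the masked assessor.
2. Base by-arm harm summaries, and any by-arm counts given to the safety officers, on those common visits plus chart abstraction.
3. Record the source of each adverse event. Tabulate events learned only through intervention or informal contact separately, and continue to evaluate and report them as now.

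Recruitment began in August 2016 (*Trial status*), so some data will predate the change. For those, tabulate by source wherever the source was recorded.

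The cost is small, because the visits already take place: a slightly longer brief visit and one more column in the safety report.

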### Frequency and plans for auditing trial conduct {23}

The trial includes close monitoring by the PI/Co-Is, IRBs, and two external safety officers. Annual progress reports are provided to the sponsor and IRBs. Sponsor or other external site visitor audits are not planned.

### Plans for communicating important protocol amendments to relevant parties (e.g., trial participants, ethical committees) {25}

Any changes to the eligibility criteria, outcomes, or analyses are reviewed by the IRB and updated in ClinicalTrials.gov.

### Dissemination plans {31a}

The results of the trial will be presented at professional conferences and local community events and shared via ClinicalTrials.gov and formal publications and furthermore to the general public through social media outlets. A summary of the primary outcome findings will be created in English and Spanish and shared with the study participants.

## Discussion

GDM is recognized as a major adverse perinatal outcome and has been linked with a range of maternal and child complications and poor outcomes, including long-term development of type 2 diabetes. Recurrent GDM affects about 66–80% of women with obesity [19, 57, 58] and increases the number of maternal and child health risks significantly [18–27]. Additionally, identification and treatment of GDM exact a high cost to the health care system [169–171]. Preventing GDM and its recurrence has been identified as a national health priority [172, 173].

To date, efforts to prevent GDM have focused primarily on interventions occurring during pregnancy, and these have met with limited success [54, 60–65]. Promising, preliminary research from epidemiologic and retrospective bariatric surgery studies suggests that reductions in body weight before pregnancy may hold the key to the prevention of GDM and its recurrence [33–39]. Emergent research suggests that it is feasible to recruit women before pregnancy and promote significant weight loss prior to conception [40, 41]. A lifestyle intervention before pregnancy in women with prior GDM may capitalize on a “teachable moment” when women appear more motivated to engage in behavior changes to prevent the recurrence of GDM in a subsequent pregnancy [42–45]. However, a fully powered trial to test the effects of maternal lifestyle intervention before pregnancy to reduce body weight and prevent GDM recurrence has never been conducted.

The Gestational Diabetes Prevention/Prevención de la Diabetes Gestacional is the first trial designed to determine whether preconception weight loss can prevent GDM recurrence in a diverse population of Hispanic and non-Hispanic women who are disproportionately impacted by GDM [57, 174, 175]. The SCT-based intervention is uniquely designed to capitalize on the potential “teachable moment” for women with prior GDM who report high motivation to change behaviors to prevent GDM recurrence and protect the health of their future baby [42–45]. The study’s battery of measures before pregnancy will provide the first comprehensive picture of how maternal weight, diet, activity, and physiology *before pregnancy* impact GDM, insulin resistance, and cardiometabolic health. The study is providing a new scientific framework for future pre-pregnancy trials by informing optimal methods for reaching women before pregnancy and the best timing, content, and duration of effective GDM prevention interventions. The American College of Obstetricians and Gynecologists (ACOG), the National Academy of Medicine, and other governmental bodies and researchers [172, 173, 176–182] have identified the interconception interval as one of the best potential times for weight control intervention to minimize the risk of a GDM and its recurrence. If successful, the results of this study will yield a novel, empirically based intervention that can be used during the interconception period to prevent GDM.

## Trial status

Protocol version 1.0; February 15, 2021. Recruitment was initiated in August 2016, and the approximate date for completion considering delays due to the COVID-19 pandemic is December 2021.

## Abbreviations

NAS: National Academy of Science
BMI: Body mass index
OGTT: Oral glucose tolerance test
